#### Descriptive analysis

We will summarize participant baseline characteristics and outcomes using means and standard deviations (SD) for continuous variables and proportions for categorical variables.

#### Inferential analysis

We will perform a primary analysis including all randomized participants. We will exclude participants who take less than 6 min to complete the survey. For the outcome of understanding, we will use *χ*^2^ tests and risk difference with 95% CIs to compare the proportion of correct responses between groups. For the outcomes of accessibility and satisfaction, we will use *t*-tests and mean differences 95% confidence intervals (95% CIs) to compare means and SDs between the intervention and control groups. Finally, we will present preference as mean (SD) overall and for both trial arms. Skewness, Shapiro-Wilk tests, and histograms will be used to evaluate whether the distribution was shifted toward the same preference in both groups. Levene’s test of equal variances will be used for all *t*-tests and degrees of freedom will be adjusted for *p* < 0.05. We will report all *p*-values to three decimal places, with values less than 0.001 reported as < 0.001. We will consider statistical significance at *p* < 0.05. Furthermore, we will conduct a meta-analysis across the three trials by combining results of the three trials. Our a priori hypothesis is that there is no difference across the three populations despite the differences in population characteristics and slight difference in the presentation formats for each population. However, we will explore differences between trials applying the GRADE approach to evaluating inconsistency which includes the chi-square test, the *I*^2^ value, the overlap in confidence intervals, and the differences in the point estimates of effect for all outcomes [29].

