### Outcomes

#### Primary outcome

##### Understanding

We define understanding as the comprehension of key guideline content (e.g., year of publication, intent of recommendation, direction of recommendation, etc.). This outcome will be measured using seven multiple-choice questions about key concepts in the recommendation with four to six response options for each question and only one correct answer (total minimum score of 0, maximum score of 7). Based on previous work, we aim to detect a difference of 10% in understanding between groups which we consider an important difference (an average difference of 1 correct answer) [18, 19, 21–23].

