### Sample size calculation

The sample size was calculated using the primary outcome of understanding. For this two-sided (*α* = 0.05) superiority analysis, these computations were made based on a *t*-test with the null hypothesis that there is no difference between the PLR version and the SLV in understanding of information.*H*_*0*_*:* PLR version = SLV*H*_*1*_*:* PLR version ≠ SLV

We will determine whether we can reject the null hypothesis of no difference in understanding between the formats of presenting recommendations. We assume a correct response rate (regarding the understanding of information) of 75% in the PLR arm and 60% in the control arm [relative risk =1.25] based on a recent RCT and prior trials on plain language summaries (PLS) of summary of findings table [19, 23]. With typical alpha (0.05) and beta (0.8) parameters and an allocation ratio of 1:1, 240 participants (120 in each arm) would be required (Stata/SE 16.0) [27]. Assuming 15% non-completion, we will recruit 282 participants from each population and adjust this number if non-completion is higher.

Since we are using two different recommendation topics with each population, we might observe an interaction between the recommendation topic and our outcome of understanding. Thus, when we reach half of our intended sample size, we will conduct an interim analysis for a possible interaction effect. If the data suggests that there might be an interaction, we will consider modifying our initial sample size. This new sample size cannot be determined in advance since we cannot anticipate the magnitude of the potential interaction effect, but it will be determined based on published guidance on power calculations for credible subgroup effects [28]. If needed, we will submit an amendment that explains the new sample size and need for additional recruitment based on the magnitude of the interaction effect identified. In summary, an enhanced sample size, if indicated and feasible, will allow us to conduct a more meaningful analysis by exploring the results by topic of recommendation.

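### The primary chi-square on proportion correct does not match the 0–7 participant score or the t-test behind the sample size, and its unit of analysis is undefined

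*Protocol article*

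**What the plan says.** Three places in the protocol article describe the primary outcome.

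- **Primary outcome, Understanding.** "This outcome will be measured using seven multiple-choice questions about key concepts in the recommendation", with one correct option each, giving a "total minimum score of 0, maximum score of 7". The target is also on the score scale: "we aim to detect a difference of 10% in understanding between groups which we consider an important difference (an average difference of 1 correct answer").
- **Sample size calculation.** "For this two-sided (*α* = 0.05) superiority analysis", "these computations were made based on a *t*-test with the null hypothesis that there is no difference" between formats. The only effect inputs are correct-response rates "of 75% in the PLR arm and 60% in the control arm". No SD is given. The result is 240 participants, 120 per arm.
- **Inferential analysis.** Understanding is to be analysed by chi-square "tests and risk difference with 95% CIs to compare the proportion of correct responses between groups". The next sentence assigns t-tests and mean differences to accessibility and satisfaction. Significance is set at p < 0.05.

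The article does not name the unit of analysis for the chi-square, mentions no allowance for seven answers coming from one person, and gives no cut-off for classing a participant as having understood.

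**The concern.** The outcome is a participant score and the important difference is a mean difference, but the test is one for proportions. The chi-square can be read in three ways:

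1. **Answers pooled over questions.** Seven answers from one person are counted as seven independent observations.
2. **One chi-square per question.** There are seven primary tests, no rule for combining them and no single primary result.
3. **Each participant classed as understanding or not.** Clustering is no problem, but no cut-off is defined and the 0–7 score is discarded.

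None of these analyses the endpoint as defined, and leaving the unit open allows it to be chosen after the data are seen. The same analysis serves three trials and feeds the planned meta-analysis. If answers are pooled and the standard errors come out too small, the combined interval is too narrow. The planned between-trial checks (chi-square, I², overlap of intervals) would also tend to show inconsistency that is not there.

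**Working it through.** **Inputs from the article:** seven items per person; score 0–7; 120 per arm; rates 75% and 60%; two-sided α = 0.05; power 0.8; 15% non-completion. **Assumed, because the article does not give them:** the within-person correlation of answers (ICC) and the difficulty of each item.

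**1. The plan's own figure.** The t-test calculation cannot be reproduced without an SD. Working backwards with SD = difference / [(1.960 + 0.842) × √(2/120)], 120 per arm implies:

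- SD 2.90 for 0.15 × 7 = 1.05 answers
- SD 2.76 for 1 answer
- SD 1.94 for 10% of 7 = 0.7 answer

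At a mean of 67.5% correct with equally difficult items, SD = √[7 × 0.675 × 0.325 × (1 + 6 × ICC)]. That is 1.57, 1.84 and 2.07 at ICC 0.1, 0.2 and 0.3, and only 2.83 at ICC 0.7. A t-test on the score for 1.05 answers is therefore an unlikely source of 120 per arm. A two-proportion formula with one unit per participant gives 152 per arm two-sided, and exactly 120 one-sided; that sidedness mismatch is a separate point. The recruitment figure does reproduce: 240 / 0.85 = 282.4.

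**2. Pooled answers, equal difficulty.** Each arm has 7 × 120 = 840 answers. The design effect is DE = 1 + 6 × ICC, and the true type I error is 2 × [1 − Φ(1.96/√DE)].

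| ICC | DE | Type I error | Naive CI width / correct width (1/√DE) |
|---|---|---|---|
| 0 | 1.0 | 5.0% | 1.00 |
| 0.1 | 1.6 | 12.1% | 0.79 |
| 0.2 | 2.2 | 18.6% | 0.67 |
| 0.3 | 2.8 | 24.2% | 0.60 |

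**3. Pooled answers, unequal difficulty.** The pooled chi-square uses variance 7 × p̄(1 − p̄) per person. With independent answers the true variance is Σpⱼ(1 − pⱼ), which is smaller when the pⱼ differ. For items at 30, 45, 55, 65, 75, 85 and 92% correct, p̄ = 4.47/7 = 0.639. The two variances are 1.616 and 1.321, a ratio of 0.82, so with no correlation the error is 2 × [1 − Φ(1.96/√0.82)] ≈ 3.0%. Correlation works in the other direction. Simulation (20,000 runs per scenario, 120 per arm, no true difference) gave:

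| Latent correlation | All items 67.5% | Items 30–92% | Items 10–98% |
|---|---|---|---|
| 0 | 5.2% | 3.0% | 1.0% |
| 0.1 | 9.3% | 6.0% | 1.9% |
| 0.3 | 17.2% | 12.0% | 4.3% |
| 0.5 | 25.6% | 18.2% | 7.4% |

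Latent correlation is not the ICC of step 2: with all items at 67.5%, latent 0.1, 0.3 and 0.5 correspond to a correlation between answers of about 0.06, 0.18 and 0.32. A t-test on the 0–7 score stayed between 4.7% and 5.2% in every scenario.

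**4. One test per question.** Each test holds 5%, but the chance of at least one false positive is 1 − 0.95⁷ = 30.2% if the tests are independent, and less if they are positively correlated.

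**The case against.** A reader might infer that the plan pools answers and that type I error is therefore well above 5%. The article does not support that as a flat statement, for three reasons.

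- It never says answers are pooled. The plural form of the test fits one chi-square per question just as well. The sample size also points away from pooling: if single answers were the units, the 152 per arm from the two-sided formula would be about 152/7 ≈ 22 participants per arm, not 120.
- The 12–24% range needs an ICC that the article does not give.
- It also needs equally difficult items. The questions cover unlike content, such as publication year and the direction of the recommendation, so unequal difficulty is plausible, and with it the error can be at or below 5%.

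A reader might also infer that pooling would give these trials too much weight in the meta-analysis. That does not follow. Only these three trials are combined, with the same kind of instrument and the same target size, so a similar understatement of variance leaves their relative weights roughly unchanged. What remains is an interval that is too narrow and distorted inconsistency checks.

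Finally, this is a journal article and a full protocol exists, so silence on clustering or multiplicity is weak evidence that they are ignored. That is fair, but the finding does not depend on silence. The article states the outcome, the sample-size test and the analysis, and the three do not agree. Some positive correlation is also to be expected on the article's own account, since Selection criteria anticipates variation in English proficiency and health literacy, which would affect all of a person's answers.

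**Conclusion.** The concern holds in conditional form. The mismatch between the 0–7 score, the t-test basis and the chi-square is certain from the text, as is the undefined unit. The size of the error depends on the reading:

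- **Pooled answers:** type I error may exceed 5%, at about 12%, 19% and 24% for an assumed ICC of 0.1, 0.2 and 0.3 with equal item difficulty. It was about 1% to 18% in the unequal-difficulty scenarios. The nominal 5% is not assured in either direction.
- **Per-question tests:** family-wise error up to about 30% under independence, with no single primary result.
- **Participant dichotomy:** no inflation from clustering, but it cannot be carried out without a cut-off.

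Because this is the primary analysis of all three trials, it should be settled before any data are analysed by arm.

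**What to change.** 1. In Inferential analysis, make the primary analysis a participant-level comparison of the 0–7 score: a t-test or linear regression of score on format, reporting the mean difference with 95% CI and also as a percentage of 7. Carry that estimate and its standard error into the meta-analysis.
2. Keep per-question proportions as descriptive displays. If an item-level risk difference is wanted, obtain it by GEE or with cluster-robust standard errors by participant.
3. Restate the sample-size basis for the score with an assumed SD, and settle the target difference, since 10% of 7 is 0.7 answer whereas 1 answer is 14.3%. The choice matters. With the equal-difficulty SDs above, 120 per arm gives at least 97% power for 1.05 answers at ICC 0.1 to 0.3, but 93%, 84% and 74% for 0.7 answer at ICC 0.1, 0.2 and 0.3.

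The cost is an amendment to the wording and a new sample-size justification, using the same survey data. Intervals will probably be wider than those from naive pooling, though not necessarily if item difficulties differ widely.

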## Objectives

The objective of this study is to compare end-users’ (youth, parents, and adult populations) understanding, accessibility and usability, satisfaction, intention to implement, and preference for COVID-19 recommendations when presented as plain language recommendation summaries (PLRs) versus standard language versions (SLVs). We hypothesize that there will be a difference in understanding of information between the two formats. We also aim to understand the reasons for their choices through our linked qualitative research.

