##### Preference

We define preference as a greater liking of one format over the other (PLR or SLV). After participants complete the tasks in the group they are randomized to, they will be asked to compare the PLR and the SLV formats. Participants will review the alternative format and indicate their preference for one of the two formats using a 7-point Likert-type scale (1 being strongly preferring the SLV, 4 being the same preference for both, and 7 being strongly preferring PLR). Participants will also have the chance to explain their choice in a text box.

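### Skewness and Shapiro-Wilk are named to judge whether preference is shifted, but neither measures a shift from neutral or a difference between arms

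*Protocol article*

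**What the plan says.** The Objectives section of the protocol article includes preference among the outcomes on which the two formats are compared: "intention to implement, and preference for COVID-19 recommendations when presented as plain language recommendation summaries (PLRs) versus standard language versions (SLVs".

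Under Preference, participants finish the tasks for their allocated format, then review the other one and "indicate their preference for one of the two formats using a 7-point Likert-type scale". The anchors are "1 being strongly preferring the SLV, 4 being the same preference for both, and 7 being strongly preferring PLR". The scale therefore has a direction and a stated neutral point, 4.

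Under Inferential analysis, "we will present preference as mean (SD) overall and for both trial arms", followed by: "Skewness, Shapiro-Wilk tests, and histograms will be used to evaluate whether the distribution was shifted toward the same preference in both groups". The same section gives accessibility and satisfaction t-tests and mean differences with 95% CIs. It names no interval or test for preference against 4, or between arms. All p-values are to be reported, and "We will consider statistical significance at" p < 0.05.

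**The concern.** The sentence on shift can be read in two ways: that both arms move toward 4, the point labelled as equal preference, or that both arms lean toward the same format. Under either reading the question is where the distribution sits, relative to 4 or relative to the other arm.

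Shapiro-Wilk and skewness are measures of shape. Adding a constant to every response changes neither of them. Two of the three tools named are therefore given a job they cannot do, and one of those two, Shapiro-Wilk, is the only formal test attached to preference. At the planned sample size its p-value will be below 0.05 almost whatever participants prefer. At stake is the inferential statement on one secondary outcome.

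**Working it through.** **Inputs.**
- Scale 1 to 7, neutral value 4 (Preference).
- n = 120 per arm and 240 per population (Sample size calculation). The protocol gives no sample size or other figure for preference, so there is none to reproduce; these are the numbers at which the tests would be run. n = 60 was also tried.
- Level 0.05, two-sided.
- Mean and SD of preference are not given. Assumed range: true mean about 3 to 5.25, SD about 1.0 to 2.5.

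**What each quantity depends on.**
- Shapiro-Wilk: W = (Σ aᵢ x₍ᵢ₎)² / Σ (xᵢ − x̄)². The weights aᵢ sum to zero, so W is unchanged when every x is replaced by x + c.
- Skewness: g = [Σ (xᵢ − x̄)³ / n] / s³. It is also unchanged by x + c.
- One-sample t: t = (x̄ − 4) / (s / √n). This does depend on 4.

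An example by hand: responses uniform on 1 to 7 have mean 4, variance (7² − 1)/12 = 4, SD 2 and skewness 0. Preference is exactly neutral, yet the shape is far from normal.

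**Simulation.** 2,000 samples per case, with the share at p < 0.05. Discretised normals are cut at 1.5, 2.5, …, 6.5. The bimodal case has probabilities .30, .12, .05, .06, .05, .12, .30. The skewed case has 0, .10, .40, .20, .12, .10, .08. The protocol names skewness but no test of it, so a standard skewness test stands in for it here.

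| Case | Mean | SD | Skewness | Shapiro-Wilk, n=120 / 240 | Skewness test, n=120 / 240 | t against 4, n=120 / 240 |
|---|---|---|---|---|---|---|
| Neutral, discretised normal | 4.00 | 1.04 | 0 | 100% / 100% | 3.5% / 3.8% | 4.5% / 5.3% |
| Neutral, discretised normal | 4.00 | 1.47 | 0 | 100% / 100% | 0.3% / 0.2% | 4.5% / 5.5% |
| Neutral, discretised normal | 4.00 | 1.79 | 0 | 100% / 100% | 0.1% / 0.2% | 4.7% / 4.6% |
| Neutral, uniform | 4.00 | 2.00 | 0 | 100% / 100% | 0.1% / 0.1% | 4.9% / 5.3% |
| Neutral, symmetric bimodal | 4.00 | 2.54 | 0 | 100% / 100% | 1.1% / 0.9% | 5.2% / 5.0% |
| Shift to PLR | 4.99 | 1.02 | −0.10 | 100% / 100% | 4.4% / 6.4% | 100% / 100% |
| Shift to PLR | 4.94 | 1.41 | −0.33 | 100% / 100% | 22.8% / 56.8% | 100% / 100% |
| Shift to PLR | 5.25 | 1.62 | −0.67 | 100% / 100% | 93.1% / 100% | 100% / 100% |
| Shift to SLV | 3.01 | 1.02 | 0.10 | 100% / 100% | 2.9% / 6.0% | 100% / 100% |
| Nearly neutral, skewed | 3.96 | 1.43 | 0.73 | 100% / 100% | 97.6% / 100% | 6.5% / 8.3% |

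Shapiro-Wilk also rejected in 100% of samples of 60 in every case. It gives the same answer for neutral and shifted preference.

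Skewness picks up a shift only when responses pile up near the end of the scale, as with the mean of 5.25. It misses a shift of about one point when the spread is small, and it flags an asymmetric distribution centred close to 4.

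**Precision of the replacement.** The 95% half-width is 1.96 × SD / √n for a mean and 1.96 × SD × √(2/120) for the difference between arms.

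| SD | Mean, n=120 | Mean, n=240 | Difference, 120 v 120 |
|---|---|---|---|
| 1.0 | 0.18 | 0.13 | 0.25 |
| 1.5 | 0.27 | 0.19 | 0.38 |
| 2.0 | 0.36 | 0.25 | 0.51 |
| 2.5 | 0.45 | 0.32 | 0.63 |

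**The case against.** A reader might infer that the plan cannot say which format is preferred. The protocol does not support that. It plans the mean and SD overall and by arm on a scale whose anchors give direction; a mean of 5.5 in each arm would point to the PLR, and with n a reader could compute an interval. Histograms, the third tool in the sentence, do show where responses lie relative to 4 and whether both arms lean the same way. Free-text reasons and interviews add context. All of this stands.

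A reader might also infer that a significant Shapiro-Wilk result will be declared a shift. No such decision rule is written; the three tools are to be used together. The simulation shows that the test is uninformative here, not that a false conclusion must follow.

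It can further be said that intervals are implied, because a meta-analysis covers secondary outcomes and consistency across trials is to be judged partly by whether confidence intervals overlap. That is fair as far as it goes, but no effect measure is named for preference.

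Finally, a separate analysis plan may exist, so the mere absence of a one-sample test would not be a finding. What remains is a mismatch that the protocol itself states: a purpose, and two tools that cannot serve it.

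**Conclusion.** The point holds in this limited form. Skewness and Shapiro-Wilk do not measure a shift from 4 or a difference between arms, so what the protocol usefully specifies for preference is descriptive only. At 120 to 240 participants Shapiro-Wilk rejected in 100% of samples in all ten cases, five of them exactly neutral and symmetric. Comparing the mean with 4 rejected in 4.5% to 5.5% of samples from those five and in 100% of samples from the four shifted cases.

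The distributions are assumed, because the protocol gives no mean or SD for preference. That both measures ignore location is a matter of definition and does not rest on them; the rejection rates do. Preference is secondary, and the conclusion on understanding is not touched.

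**What to change.** In the sentence under Inferential analysis, remove skewness and Shapiro-Wilk as the means of evaluating shift. Put in their place:
- mean preference minus 4 with its 95% CI, within each arm and overall;
- the difference between arms in mean preference with its 95% CI. Arm determines which format was read first, so this shows whether the preference depends on the order of reading.

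Keep the histograms as description. A signed-rank sensitivity analysis or equal weighting of the arms in the overall mean is optional; with 1:1 allocation, weighting would change little.

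The cost is one reworded sentence. Recruitment has begun, so it belongs in an amendment posted by the route that the protocol already names, preferably before the allocation labels are revealed. No new data, participants or survey questions are needed.

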### Statistical analysis

Only participants who submit a complete good quality survey will be included in the analysis. We will exclude all incomplete, speeding (less than 6 min to completion), and straight-lining responses. Each population’s results will be analyzed separately, and we will explore subgroup effects within each group. These subgroups are the topic of recommendation, health literacy level, and English proficiency level of participants. We will also pool the results across populations and conduct a meta-analysis for our primary outcome of “understanding” and other secondary outcomes. In the final analysis, after pooling the results, we will explore for potential interaction related to the recommendation topic and participants’ health literacy level. We will conduct the analyses using IBM SPSS® (Statistical Package for Social Sciences) version 23.

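### Choosing the t-test for accessibility and satisfaction by a Levene pre-test lets type I error drift slightly from 5% if arm sizes and SDs both differ; using Welch throughout removes this at almost no cost

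*Protocol article*

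**What the plan says.** Under Inferential analysis, the protocol article assigns t-tests to two secondary outcomes: "For the outcomes of accessibility and satisfaction, we will use" t-tests and mean differences with 95% confidence intervals. It then states that Levene's "test of equal variances will be used for all" t-tests and that "degrees of freedom will be adjusted for" p < 0.05. With SPSS as the named software, I read this as taking the equal-variance row of the output unless Levene is significant, and the unequal-variance (Welch) row otherwise. Significance is set at p < 0.05.

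The primary outcome, understanding, has no Levene step. It is compared by chi-square and "risk difference with 95% CIs to compare the proportion of correct responses between groups".

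Two other statements bear on arm sizes. Randomisation is 1:1, with 120 per arm planned and 282 recruited per population to allow for 15% non-completion (Sample size calculation). Under Statistical analysis, "Only participants who submit a complete good quality survey will be included in the analysis": incomplete, speeding and straight-lined responses are dropped after randomisation. That section also names subgroups by topic, health literacy and English proficiency.

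**The concern.** A non-significant Levene test does not show that the variances are equal. When it misses a real difference, the pooled standard error is kept. That standard error is wrong when the arms also differ in size: too small if the smaller arm is the more variable, too large in the opposite case.

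The arms read different documents, an original guideline PDF or a plain language summary, so completion and reading times could differ between them and the exclusions could fall unevenly. The article gives no figures on this. At stake are the coverage of the accessibility and satisfaction intervals and the error rate of their tests. There is also a loss of simplicity, since the variance formula could change from outcome to outcome and from trial to trial on the result of a noisy pre-test.

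**Working it through.** **Inputs from the article.** Levene threshold 0.05; significance level 0.05; 120 per arm; 282 recruited, which reproduces as 240/0.85 = 282.4. The article states no error rate for the two-stage rule beyond the nominal 5%, and no SDs.

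**Assumed inputs.** SD ratios of 1.1 to 1.3, and unequal arm splits. The 141/99 split puts the whole 15% loss in one arm: 282/2 = 141, and 0.15 × 282 ≈ 42, so 141 − 42 = 99. The 130/90, 65/40 and 45/65 splits are illustrative, the last two at about the size of a topic subgroup.

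**Step 1: why equal arms are safe.** The pooled squared standard error is s²p(1/n₁ + 1/n₂), with s²p = [(n₁−1)s₁² + (n₂−1)s₂²]/(n₁+n₂−2). With n₁ = n₂ = n it reduces to (s₁² + s₂²)/n, which equals the unequal-variance form s₁²/n₁ + s₂²/n₂. A Levene miss at 120/120 therefore leaves the standard error unchanged.

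**Step 2: size of the pooled error with unequal arms.**
- 99/141, SDs 1.2 and 1: s²p = (98×1.44 + 140)/238 = 1.181. Pooled: 1.181×(1/99 + 1/141) = 0.02031. True: 1.44/99 + 1/141 = 0.02164. Ratio of standard errors √(0.02031/0.02164) = 0.969, so 3% too small.
- 40/65, SDs 1.3 and 1: s²p = (39×1.69 + 64)/103 = 1.261. Pooled 0.05094, true 0.05763, ratio 0.940, so 6% too small.
- 45/65, SDs 1 and 1.3: s²p = (44 + 64×1.69)/108 = 1.409. Pooled 0.05298, true 0.04822, ratio 1.048, so 5% too large.

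**Step 3: how often Levene detects the difference.** At 120/120 with normal data it rejects in 16% of trials at SD ratio 1.1, 46% at 1.2, 76% at 1.3 and 98% at 1.5.

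**Step 4: type I error.** Simulated normal data with equal means, two-sided 5%, 400,000 trials per row (Monte Carlo standard error about 0.03 points):

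| Arms (SDs) | Levene rejects | Always pooled | Two-stage rule | Welch |
|---|---|---|---|---|
| 120/120 (1, 1.2) | 45% | 5.0% | 5.0% | 5.0% |
| 99/141 (1.1, 1) | 16% | 5.4% | 5.2% | 5.0% |
| 99/141 (1.2, 1) | 45% | 5.8% | 5.3% | 5.0% |
| 99/141 (1, 1.2) | 44% | 4.3% | 4.7% | 5.0% |
| 90/130 (1.2, 1) | 42% | 5.8% | 5.3% | 5.0% |
| 40/65 (1.3, 1) | 40% | 6.5% | 5.6% | 5.0% |
| 45/65 (1, 1.3) | 41% | 4.1% | 4.6% | 5.0% |

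Separate simulations of the same settings agree to about 0.1 point (for example 5.7% at 40/65 and 5.35% at 90/130). Interval coverage is the complement, for example 100 − 5.3 = 94.7%.

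**Step 5: bounded data.** Averages of six 7-point items (inter-item correlation of 0.6 assumed, 20,000 trials, SD ratio about 1.27) show the same pattern at 65/40 and 40/65. The two-stage rule gives 5.4% and 4.6%; Welch gives 4.8% and 5.1%.

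**Step 6: cost of Welch when variances are equal.** At a standardised difference of 0.364 (about 80% power at 120 per arm), power is 80.10% against 80.11% at 120/120, 78.91% against 78.93% at 99/141, and 77.29% against 77.44% at 90/150. The largest loss is 77.44 − 77.29 = 0.15 points.

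**The case against.** The case for leaving the text alone is substantial. The rule is pre-specified and deals with unequal variances. It also removes most of the distortion: at 80/160, always pooling would range from 2.6% to 8.4%, while the two-stage rule stays within 4.3% to 5.6%. At the planned design there is no effect at all. Harm needs unequal arms, unequal SDs and a Levene miss together, and the article supports none of the assumed values. A 130/90 split from 141 per arm would mean losing 8% in one arm (11/141) and 36% in the other (51/141), against a planning figure of 15% overall. The subgroup figures also presume separate t-tests within topic, whereas the article says only that subgroup effects will be explored.

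All of this stands and limits the size of the point. It gives no reason to prefer the pre-test, which offers at most 0.15 points of power in return.

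Two stronger readings are tempting. One is that uneven survey loss by itself shifts the error rate. It does not: the direction and size depend jointly on which arm is smaller and which is more variable, and with equal SDs the two-stage rule stays near 5%. The other is that the primary result is affected, because the sample size section bases its computation on a t-test. The Inferential analysis section assigns chi-square and a risk difference to understanding, so as written the Levene rule does not reach it.

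**Conclusion.** The point holds as a small improvement to a stated rule. It is not an error that would be expected to change a conclusion. The effect is nil at 120/120. It is about 0.2 to 0.4 points above 5% at 141/99 or 130/90 with the smaller arm more variable, about 0.7 points above in an assumed 65/40 subgroup, and about 0.4 points below at 45/65 with the larger arm more variable. Welch stays at about 5.0% to 5.1% in these settings. Only accessibility and satisfaction are concerned. The figures rest on assumed arm splits, SD ratios of 1.1 to 1.3 and mainly normal data, and on reading the degrees-of-freedom adjustment as SPSS's unequal-variance row.

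**What to change.** Replace the Levene sentence under Inferential analysis with:

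> All t-tests and confidence intervals for mean differences use the unequal-variance (Welch) form, without a preliminary test of variances.

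The cost is one sentence. Data collection, software and sample size do not change, because SPSS already prints the unequal-variance row. The power given up is at most about 0.15 points in the settings checked.
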